# Repetitive transcranial magnetic stimulation for depression after basal ganglia ischaemic stroke: protocol for a multicentre randomised double-blind placebo-controlled trial

**DOI:** 10.1136/bmjopen-2017-018011

**Published:** 2018-02-03

**Keywords:** repetitive transcranial magnetic stimulation, post-stroke depression, ischemic stroke

## Abstract

**Introduction:**

Studies suggest that repetitive transcranial magnetic stimulation (rTMS) is effective for the treatment of depression and promotes the repair of white matter. This study aims to assess the effectiveness of rTMS in treating depression after basal ganglia ischaemic stroke and to examine whether such effects are related to restoration of white matter integrity.

**Methods and analysis:**

Sixty-six participants will be recruited from Zhujiang Hospital, Nanfang Hospital and Sichuan Bayi Rehabilitation Hospital and randomised in a 1:1 ratio to receive active rTMS treatment or sham rTMS treatment in addition to routine supportive treatments. The data will be collected at 0, 2 and 4 weeks after the commencement of treatment. The primary outcome is the measurement of 24-item Hamilton Depression Rating Scale scores, and the secondary outcomes include diffusion tensor imaging results and the results of neuropsychological tests including the National Institutes of Health Stroke Scale, Activities of Daily Living Scale, Montreal Cognitive Assessment, Clinical Global Impressions scales, Aphasia Battery in Chinese, Social Support Revalued Scale and Medical Coping Modes Questionnaire.

**Ethics and dissemination:**

This study has been approved by the Ethics Committee of Zhujiang Hospital of Southern Medical University. The findings will be disseminated by publication in a peer-reviewed journal and by presentation at international conferences.

**Trial registration number:**

NCT03159351.

Strengths and limitations of this studyThe trial will focus on the efficacy of repetitive transcranial magnetic stimulation (rTMS) in patients with post-stroke depression (PSD) with the purpose of providing a mature approach to the treatment of PSD.It will explore the effect of high-frequency stimulation on the left and low-frequency stimulation on the right dorsolateral prefrontal cortex in patients with PSD, aiming to obtain a higher level of evidence for the stimulation parameter settings in rTMS treatment of patients with PSD.Non-invasive diffusion tensor imaging based on objective assessment of nerve fibres will be used to evaluate the therapeutic effect of rTMS on PSD.The patients will receive only short-term treatment and will be followed up for 1 month.Participants from only two provinces in China will be included.

## Introduction

### Background and rationale

Stroke is a global health problem and, in 2015, the number of deaths related to stroke reached 6.326 million around the world, among which 45.89% were attributed to ischaemic stroke.^1^ Depression occurs frequently in stroke survivors and has a significant impact on post-stroke rehabilitation.^2^ The conventional treatment of post-stroke depression (PSD) relies on supportive therapy and medications, but a proportion of patients can remain refractory to treatment.^3^ Studies have shown that repetitive transcranial magnetic stimulation (rTMS) has a definite antidepressant effect on major depression,^4^ and a recent meta-analysis also suggests the beneficial effects of rTMS on PSD, but such studies should be carefully examined for their heterogeneity and potential biases.^5^ To our knowledge, no studies have been reported that examine the effect of rTMS on PSD in China, and the mechanism by which rTMS improves PSD remains to be clarified. In addition, the stimulation parameter settings in rTMS treatment still await standardisation, and it is difficult to determine the optimal frequency (between 5 Hz and 20 Hz) in high-frequency rTMS of the left dorsolateral prefrontal cortex (DLPFC).

The basal ganglia area is the predilection site of stroke. This area, which is not an exact anatomical concept but one originating from neuroimaging, consists of the basal ganglia, the capsula interna and the surrounding white matter^6^; in other words, the basal ganglia area covers most of the subcortical structures that constitute the limbic–cortical–striatal–pallidal–thalamic (LCSPT) circuit.^7^ The limbic system is known to be closely related with emotional regulation,^8^ and as the LCSPT circuit is the most important part of the limbic system, LCSPT dysfunctions are thought to contribute to the occurrence of depression.^9^ Investigators reported a high incidence of depression after cerebral infarction in the basal ganglia area.^10^ Our group previously found that structural damage of the LCSPT circuit, as a result of white matter damage following cerebral infarction in the basal ganglia area, was associated with a high likelihood of PSD.^11^ The nuclei in the LCSPT circuit are connected via nerve fibres, and damage to these nerve fibres disrupts the integrity of the white matter as shown by MRI.^12^

As numerous studies have demonstrated the beneficial effect of rTMS treatment on white matter integrity,^13–15^ we hypothesised that the antidepressant effect of rTMS in patients with depression following cerebral infarction in the basal ganglia area is related to its action on the LCSPT circuit. The aim of this multicentre randomised controlled trial is to assess the effectiveness of rTMS in treating PSD and to investigate the role of the LCSPT circuit in the therapeutic effect of rTMS for PSD.

## Methods

### Study setting

The study will be conducted in two university hospitals, Zhujiang Hospital and Nanfang Hospital affiliated to Southern Medical University (Guangzhou, China) and in Sichuan Provincial Bayi Rehabilitation Hospital, a general hospital in Chengdu, China. The patients will be assessed for enrolment, and eligible patients will be hospitalised for treatment in the departments of neurology in the three hospitals.

### Trial design

This randomised double-blind placebo-controlled multicentre superiority trial is designed to recruit two parallel groups, and randomisation will be performed by block randomisation in a 1:1 allocation ratio. The study design is shown in the flow chart in figure 1.

**Figure 1 F1:**
[figure not shown]
Flow chart of the trial design.

### Participant enrolment and eligibility criteria

The participants will be recruited by advertisement on the internet and using posters in hospitals. Potential eligible patients will be screened for enrolment according to the inclusion and exclusion criteria listed in table 1.

**Table 1 T1:** Inclusion and exclusion criteria

Criteria	Description
Inclusion criteria	First-time ischaemic stroke with clinical and MRI or CT findings of basal ganglia ischaemic stroke and a DSM-IV diagnosis of depression due to stroke (ICD-10-CM code 293.83[F06.32]) Age 25–75 years with a recent (from 3 weeks to 3 months) ischaemic stroke Clear signs of neurological deficits in the acute phase Clear consciousness Right-handedness
Exclusion criteria	Aphasia or severe cognitive impairment, severe hearing impairment, or severe language comprehension deficits due to other causes Other cerebral diseases such as Parkinson’s disease, encephalitis, dementia, multiple sclerosis, head injury Severe systemic disease or ongoing neoplasia Ongoing postoperative recovery Prior history of depressive disorders or major trauma within 1 year, severe depression or any other severe mental disorders Current or prior antidepressant use for any reason Addiction to drugs, alcohol or other substances Contraindications of MRI scan and rTMS treatment such as pacemaker implantation, a history of epilepsy, major head trauma and seizures Pregnant or breast-feeding women Participation in other clinical research projects Refusal to sign the informed consent of this study

### Ethical considerations

This study has been approved by the Ethics Committee of Zhujiang Hospital of Southern Medical University. The methods, purpose and potential risks of this study will be fully explained to the participants and their family members. Each patient will be asked to sign three informed consents before participating in the study.

### Randomisation and blinding

For randomisation of the patients, random numbers will be generated using SAS9.4 software by statisticians based on a randomised block design with a block length of s. The magnetic stimulation coils for active and sham treatments have identical appearances and will be numbered by a statistician. The random numbers will be printed and sent to each trial centre in sealed envelopes. Upon enrolment of an eligible patient, the investigator opens the envelope to reveal the number of the magnetic stimulation coil to be used, without knowing whether the patient receives active or sham treatment. In this double-blind trial, both the participants and investigators are blinded to the nature of treatment (active or sham).

### Interventions

The participants enrolled in this trial will receive either active or sham rTMS treatment in addition to routine supportive treatments including antiplatelet agents, blood pressure control, neurotrophic therapy, physical therapy and cognitive rehabilitation prescribed based on the condition of the individual participant. The enrolled patients will not receive any other antidepressants, anxiolytics or hypnotic treatments that may have an impact on depression treatment during the study. All the participants will receive psychiatric and neuropsychological tests and MRI examination at the time of enrolment and at the end of treatment. rTMS will be performed using a Mag Pro R30 device (Mag Venture Company, Frum, Denmark) via 121 mm circular coils (MCF-125). The participants will receive active or sham treatment 5 days per week for four consecutive weeks. The motor threshold (MT) is defined as the lowest stimulation intensity capable of inducing at least 50 μV peak-to-peak amplitude of motor evoked potentials in at least half of 10 trials. The detailed parameters of the protocols of active rTMS treatment are listed in table 2.

**Table 2 T2:** Active rTMS treatment protocols

Localisation	Frequency	Intensity	Times/train	Trains	Duration	Total times
Left DLPFC	10 Hz	110% MT	200	10	40 s	20
Right DLPFC	1 Hz	100% MT	30	10	10 s	20

DLPFC, dorsolateral prefrontal cortex; MT, motor threshold.

### MRI

On enrolment and at the end of the trial, the patient will receive a MRI examination using a 3.0T PHILIPS Magnetic Trio Tim scanner. For the standard investigation, MRI will be performed using the following scan parameters for different sequences: for T1-weighted sequence, time of echo (TE) 20 ms, time of repetition (TR) 2000 ms, number of signal averaged (NSA) 1, number of slices 32, slice thickness 3 mm; for T2-weighted sequence, TE 80 ms, TR 3000 ms, NSA 2, 32 slices, slice thickness 3 mm; for FLAIR sequence, TE 80 ms, TR 3000 ms, NSA 2, 32 slices, slice thickness 3 mm; for diffusion tensor imaging (DTI) using single short echo planar imaging (SE-EPI), TE 68 ms, TR 2300 ms, NSA 1, 32 slices, slice thickness 3 mm, b_0_=0, b_1_=1000, matrix=512*512. Once the original data have been obtained, an experienced imaging physician will select the caudate nucleus, lentiform nucleus, dorsal medial nucleus of the thalamus and the nucleus of the thalamus as the regions of interest (ROIs) at the imaging layer of the basal ganglia. The three-dimensional fibre bundle imaging technique will be used to display the fibrous pathway of the dorsal basal ganglia system and the fibrous pathway of the ventral basal ganglia system. The DTI parameters will be obtained, including the fractional anisotropy (FA), apparent diffusion coefficient (ADC) and neural fibre number (NFN). The MRI scanners at the three centres will be tested for homogeneity before the trial, while ROI selection and DTI data acquisition will be performed by an experienced radiologist using PHILIP 2.1 software.

### Outcome assessment

#### Baseline assessment

Demographic data will be collected from the patients, including age, gender, height, body weight, education level, occupation and marital status. Vital signs will be measured including body temperature, pulse, respiration and blood pressure. Lesion characteristics including lateralisation and the number and size of the lesions will be recorded. Data including past history and treatment prescription, levels of blood lipids and blood glucose, liver function index and renal function index will be collected before randomisation by reviewing the medical records of the patients.

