### Secondary outcome measures

#### DTI results

Nerve fibres are important components of the LCSPT circuit apart from the cerebral cortex, corpus striatum and thalami. The nuclei are connected by abundant nerve fibres. DTI is a special sequence of MRI, which is currently the best non-invasive method to observe and track the nerve tracts. We will assess the DTI parameters of the patients including FA, ADC and NFN collected on enrolment and at the end of the trial.

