### Statistical analysis

The quantitative data including the demographic indicators, laboratory test results, MRI results and neuropsychological test results will be expressed as numbers, means with SD or median with range or quartile range as appropriate. These data will be compared using the independent sample t-test or rank-sum test depending on whether the data are normally distributed. Qualitative data, including the response and emission rates and incidence of AEs, will be expressed as frequency or frequency rate and compared using a χ^2^ test between the two groups. The missing data will be described in terms of exit data, exit reason, treatment arm, frequencies and percentage of missing data in each group and the data imbalances will be evaluated by a χ^2^ test or Fisher’s exact test. All the data will be double-entered into Epidata software and analysed using SAS software by statisticians blinded to the participants’ allocation. A P value <0.05 will be considered to indicate a statistically significant difference.

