## Discussion

The conventional treatments of PSD include selective serotonin reuptake inhibitors,^18^ tricyclic antidepressants^19^ and electroconvulsive therapy (ECT),^20^ which are not always effective. Recent evidence has shown that rTMS has antidepressant actions^21 22^ and produces therapeutic effects comparable to those of ECT.^23^ In spite of the various hypotheses that have been proposed, the exact mechanism underlying the antidepressant effect of rTMS remains unknown.^24–26^

In this trial we determined the frequency and intensity of rTMS treatment based on previous studies reporting the positive antidepressant effect of the treatment,^27–29^ and chose the settings of pulses and sessions according to an evidence-based guideline.^4^ As both high-frequency rTMS of the left DLPFC and low-frequency rTMS of the right DLPFC are recommended in the treatment of major depression, and considering that patients with PSD have more brain structural changes than those with primary depression, we chose bilateral DLPFC stimulation for rTMS treatment in this study.

Changes in white matter have an important role in the development of many neuropsychiatric diseases,^30^ including cognitive and emotional disorders.^31^ As a non-invasive imaging technique, DTI provides an important modality for evaluating white matter integrity in vivo. In DTI, the parameter FA can sensitively reflect the integrity of the white matter fibres while the ADC value allows sensitive detection of changes in the density and number of nerve fibres.^26^ Numerous studies have reported reduced FA values in the brain of patients with depression,^26 32^ and the structural and functional brain abnormalities, particularly in the LCSPT system, are thought to be associated with the occurrence of depression.^33^ Our previous study has confirmed that the occurrence of PSD was associated with neurological functional deficits following basal ganglia infarction, and the depression level was correlated with the reductions in the FA values of the bilateral pallidum and the left putamen.

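### DTI results are compared by an unadjusted two-sample test although baseline DTI and lesion side are collected, which gives up precision on the mechanistic outcome

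*Protocol article*

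**What the plan says.** All references are to the protocol article.

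- **Eligibility (Table 1):** patients need "clinical and MRI or CT findings of basal ganglia ischaemic stroke". No side is named, so left, right and bilateral lesions can enter.
- **Baseline assessment:** "Lesion characteristics including lateralisation and the number and size of the lesions will be recorded". The article does not use these data again.
- **MRI:** the person reading the scans "will select the caudate nucleus, lentiform nucleus, dorsal medial nucleus of the thalamus and the nucleus of the thalamus as the regions of interest". The regions are named by nucleus, without hemisphere and without reference to the lesion.
- **DTI results:** "We will assess the DTI parameters of the patients including FA, ADC and NFN collected on enrolment and at the end of the trial". A baseline value of each measure is therefore available.
- **Statistical analysis:** the rule covers "The quantitative data including the demographic indicators, laboratory test results, MRI results and neuropsychological test results", and states: "These data will be compared using the independent sample t-test or rank-sum test depending on whether the data are normally distributed". Normality is the only thing that changes the method.
- **Interventions (Table 2):** the left DLPFC receives 10 Hz and the right 1 Hz.
- **Discussion:** in the group's earlier study, depression level correlated with "the reductions in the FA values of the bilateral pallidum and the left putamen", a finding that was partly side-specific.

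**The concern.** Every patient has a basal ganglia infarct, and the DTI regions are basal ganglia and thalamic nuclei, so the infarct lies in or near the tissue being measured. Lesion side and the region's own baseline value are then two obvious sources of between-patient variation in end-of-treatment DTI. Both are collected before treatment, and the stated test uses neither.

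Whether any antidepressant effect is linked to white matter restoration is the trial's second stated aim, and DTI is the outcome that carries it. The trial was sized for a different endpoint. With a few dozen patients per arm, avoidable variance makes a real DTI effect easier to miss, and a null result could be misread as evidence against the circuit hypothesis. No stratification by lesion side is described, so a chance imbalance between arms would pass uncorrected into the DTI contrast.

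**Working it through.** **1. The plan's own figure.** The sample size section uses an arcsine formula with response rates 0.041 and 0.375, two-sided 5% and 90% power.

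- asin√0.375 − asin√0.041 = 0.6591 − 0.2039 = 0.4552
- n = (1.960 + 1.282)² / (2 × 0.4552²) = 10.507 / 0.4143 = 25.36, rounded up to 26 per arm

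The stated 26 is reproduced, but it sizes the response rate. The article gives no SD, effect size or power for DTI, so everything below rests on assumed values.

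**2. Lesion side, raw end values analysed by anatomical side.** Let a share p of patients have the lesion on the analysed side, and let the lesion shift the DTI value by d within-group SDs. The variance seen by the unadjusted test is 1 + p(1 − p)d². Assume p = 0.5, a true difference of 0.8 SD and 26 per arm. Power is from the noncentral t with 50 df, treating the mixture as normal.

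| d | variance 1 + 0.25d² | 26 per arm acts like | effect 0.8/√variance | power |
|---|---|---|---|---|
| 0 | 1.00 | 26 | 0.80 | 80.7% |
| 0.5 | 1.06 | 24.5 | 0.78 | 78.4% |
| 1 | 1.25 | 20.8 | 0.72 | 71.6% |
| 1.5 | 1.56 | 16.6 | 0.64 | 61.9% |
| 2 | 2.00 | 13 | 0.57 | 51.6% |

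**3. Where that loss shrinks or vanishes.**

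- *Change scores.* An offset present at both visits cancels. Then d is only the lesioned-versus-intact gap in change, so the low end of the table applies, or zero.
- *Average of both sides.* Each patient with a one-sided lesion contributes one lesioned and one intact side. The average shifts by d/2 for all of them, which adds no variance. Only patients with bilateral lesions would differ.

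**4. Chance imbalance.** Taking the lesion side of each patient as an independent 50:50 draw, the exact binomial probability that the arms differ by at least 15 percentage points in the share of left lesions is 33% at 26 per arm and 27% at 33 per arm. For at least 20 points it is 13% and 11%. In the setting of step 2, a 15-point imbalance moves the contrast by 0.15 × d: 0.15 SD at d = 1 and 0.30 SD at d = 2. This is the variance of step 2 as seen in a single trial, not a further loss.

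**5. Baseline value.** If baseline and end values have equal variance and correlation ρ (not in the documents), variance relative to raw end values is 1 − ρ² for ANCOVA and 2(1 − ρ) for change scores.

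| ρ | ANCOVA | change score |
|---|---|---|
| 0.5 | 0.75 | 1.0 |
| 0.7 | 0.51 | 0.6 |
| 0.9 | 0.19 | 0.2 |

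Since 2(1 − ρ) − (1 − ρ²) = (1 − ρ)², ANCOVA is never the less precise of the two. It therefore helps whether raw or change values were intended, which the Statistical analysis section does not say.

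**The case against.** **Detail left to an SAP.** The labelling of regions by side and the covariates for secondary outcomes are commonly settled in a full protocol or SAP, and neither is shown. This stands for the labelling. It does not stand for the test: the article names MRI results and fixes an unadjusted comparison for them.

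**Mixing of hemispheres.** A reader might infer that infarcted and intact hemispheres will be pooled. The MRI section does not say so. It states neither pooling, nor averaging, nor analysis by anatomical side, and the group's earlier FA finding was reported by side.

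**Bias.** A reader might also infer that ignoring lesion side biases the treatment comparison. Randomisation balances side in expectation, so the harm is lost precision and uncorrected chance imbalance.

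**Dilution.** It is tempting to add that intact tissue dilutes the effect. That requires an effect concentrated on the lesioned side. The documents do not say this: stimulation is bilateral, and part of the earlier FA finding was bilateral.

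**Size.** The larger losses need raw values analysed by anatomical side and a large d. The Discussion speaks of comparing DTI before and after treatment, which points towards change. Two of the four regions are thalamic, so one d for all regions is a simplification. All of this stands.

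**Lesion-relative coding.** Making the ipsilesional value the lead one would pool hemispheres stimulated at 10 Hz with hemispheres stimulated at 1 Hz, and a main effect for lesion side would not remove a treatment-by-side difference. This stands too, so that coding should not be imposed as the lead.

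**Conclusion.** The point holds as a matter of efficiency. The article commits the DTI comparison to an unadjusted test while two relevant pre-treatment variables are already in hand. The consequence is reduced precision, and no protection against chance imbalance in lesion side, on a secondary outcome that carries the mechanistic aim. The primary outcome and its sample size are untouched.

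The size is unknown. Under the assumptions of step 2, power falls from 81% to between 78% and 52% as d goes from 0.5 to 2. Under change scores or side averages, the part due to lesion side is small or nil. What baseline adjustment gains depends on the unknown ρ. The change is worth making because it costs very little, not because a large loss has been shown.

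**What to change.** In the Statistical analysis section, take DTI out of the general t-test or rank-sum rule. Compare arms on each end-of-treatment FA, ADC and NFN value by ANCOVA, adjusting for the same region's or tract's baseline value, lesion side (left, right, bilateral) and centre. Report results by hemisphere, with ipsilesional and contralesional results as a supporting presentation. Whether anatomical or lesion-relative coding leads is the sponsor's choice, because the hemispheres receive different stimulation. It should be fixed before unblinding so that the side is not chosen after seeing results.

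The cost is a change of wording, a few model degrees of freedom and a longer table. No new scans, patients or data items are needed.
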